**Discussion:**

We hypothesize that the addition of low-dose rocuronium during laryngeal mask airway-assisted flexible fiberoptic bronchoscopy under general anesthesia may optimize operation conditions, reduce coughing frequency, lower remifentanil dosage and the failure rate, stabilize hemodynamic fluctuations, minimize adverse events and enhance satisfaction, thereby providing valuable reference for clinical anesthesia practice in these procedures.

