Several studies, as documented in case reports, have reported positive experiences with the use of neuromuscular blocking agents in LMA-assisted FFB (19, 23). However, there is currently no established guideline for the recommendation of neuromuscular blocking agents during anesthesia for FFB. Barclay et al.’s study demonstrated that the addition of low-dose rocuronium (0.3 mg⋅kg^–1^, equivalent to the Effective Dose 95) to propofol and alfentanil significantly improved the conditions for tracheal intubation after the induction of anesthesia (24). Gelberg et al.’s study showed that the addition of 0.2 mg⋅kg^–1^ of rocuronium to propofol and remifentanil during anesthesia induction in infants results in improved intubation conditions compared to placebo, although the difference did not achieve statistical significance (25). Both of the aforementioned studies imply that low-dose neuromuscular blocking agents may be beneficial for airway operations.

In this randomized placebo-controlled study, we hypothesize that the combination of propofol, remifentanil, and 0.3 mg⋅kg^–1^ rocuronium will optimize the examination conditions, effectively decrease the frequency of coughing, minimize the necessary dose of remifentanil, stabilize the hemodynamic fluctuations, and enhance the satisfaction of bronchoscopists, anesthesiologists, and patients. This approach aims to provide a valuable reference for clinical anesthesia practices during these procedures.

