The secondary endpoints will be analyzed using the multivariate logistic regression model or the generalized linear model, adjusting for the same covariates as those of the primary endpoint. Repeated measurement data will be analyzed using a mixed linear model to compare haemodynamic variables and cough scores in the PACU between groups. To address the issue of multiple comparisons for adverse events observed in secondary endpoints, the Benjamini-Hochberg procedure will be employed to control the false discovery rate.

The analysis will be performed on the modified intention-to-treat population. To ensure robustness, a per-protocol analysis will additionally be conducted; however, the intention-to-treat approach will remain the primary basis for analysis. Missing data will be processed by multiple imputation and maximum likelihood method. All endpoints are performed at the two-sided 5% significance level. Statistical analyses will be performed using SPSS statistics (version 19.0; IBM SPSS, Chicago, IL, USA).

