Neuromuscular blocking agents are widely used as an anesthesia adjunct to facilitate tracheal intubation and mechanical ventilation, relax abdominal muscles, and ensure immobility during surgery (29, 30). Tips and tricks for anesthesia during pediatric rigid bronchoscopy indicate that neuromuscular blocking agents can be administered when blood pressure or other hemodynamic parameters preclude the administration of sufficient doses of anesthetic agents (31). In Dich et al.’s study, which involved 20 adult participants, total intravenous anesthesia with suxamethonium was demonstrated to be a safe technique for LMA-assisted FFB (19). A retrospective observational study conducted by Li et al. demonstrated that muscle relaxants and low-frequency conventional ventilation can be safely utilized in both flexible and rigid bronchoscopy procedures for patients with chronic airway obstruction. They found that no patients experienced ventilation failure, bronchospasm, or intraoperative coughing (23). The role of neuromuscular blocking agents in FFB remains incompletely understood. To our knowledge, this will be the first randomized controlled trial to evaluate whether the adjunctive use of low-dose rocuronium in combination with remifentanil during LMA-assisted FFB in children leads to reduced coughing, a lower remifentanil dosage, more stable hemodynamics, no impact on discharge time, and increased satisfaction among anesthesiologists, bronchoscopists and parents. The selection of rocuronium over cisatracurium represents a deliberate choice based on the specific requirements of this trial. Rocuronium at 0.3 mg⋅kg^–1^ provides a rapid-onset, moderate-depth neuromuscular blockade whose duration approximates the typical procedure time. Given the availability of sugammadex, the duration of action becomes both flexible and controllable. Any residual blockade at the end of the procedure can be fully reversed within 2–3 min. However, we acknowledge that cisatracurium offers theoretical advantages, including organ-independent metabolism and a recovery profile less influenced by temperature or hepatic and renal function. In the context of this study conducted in healthy children undergoing brief procedures with active temperature management, these advantages are considered less critical than the practical benefits of rocuronium. In addition to reducing coughing and providing improved operating conditions, the use of low-dose rocuronium may allow for a reduction in the doses of remifentanil required to achieve adequate procedural conditions. Such a reduction could translate into faster emergence from anesthesia, fewer respiratory complications in the PACU, and an overall enhanced recovery profile. For our pediatric patients, intravenous propofol at a dose of 3 mg⋅kg^–1^ in combination with remifentanil at 3 μg⋅kg^–1^ will be utilized for induction. This will be followed by the administration of either 0.3 mg⋅kg^–1^ of rocuronium or an equivalent volume of normal saline. Sevoflurane will be titrated to achieve the appropriate depth of anesthesia, while remifentanil will be continuously infused. A LMA with an interface is inserted to guide the fiberscope passage while allowing uninterrupted ventilation and maintaining oxygenation.

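### Six secondary endpoints named in the trial's hypothesis are each tested at two-sided 5% with no hierarchy or exploratory label, while multiplicity is controlled for adverse events only

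*Protocol article*

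**What the plan says.** All statements are in the protocol article.

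- **Significance level.** Statistical analysis: "All endpoints are performed at the two-sided 5% significance level".
- **Multiplicity.** The same section limits adjustment to one item: it addresses "multiple comparisons for adverse events observed in secondary endpoints", for which "the Benjamini-Hochberg procedure will be employed to control the false discovery rate".
- **Hypothesis.** The abstract's Discussion paragraph expects rocuronium to "reduce coughing frequency, lower remifentanil dosage and the failure rate, stabilize hemodynamic fluctuations, minimize adverse events and enhance satisfaction". The Introduction's hypothesis is that the combination will "effectively decrease the frequency of coughing, minimize the necessary dose of remifentanil, stabilize the hemodynamic fluctuations, and enhance the satisfaction of bronchoscopists, anesthesiologists, and patients". The Discussion presents the trial as the first randomized test of whether the drug "leads to reduced coughing, a lower remifentanil dosage, more stable hemodynamics, no impact on discharge time, and increased satisfaction among anesthesiologists, bronchoscopists and parents".
- **Secondary list.** The Secondary endpoints section has ten numbered items, nine of which are not adverse events. The numbering is not described as a testing order.

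No section gives a hierarchy, a gate on the primary result, an alpha split or an exploratory label for those nine.

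**The concern.** Unadjusted secondary endpoints under a single primary are common, and harmless while they are read as supportive. Two features make this case different.

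First, the plan recognises multiplicity, chooses a remedy and confines it to adverse events. It therefore states a rule; the matter has not simply been left to an analysis plan. An analysis plan that followed the article would carry the gap forward.

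Second, the unprotected endpoints are part of what the trial says it expects to show. With the full 5% spent on each, a chance difference in remifentanil dose or in one satisfaction score could be presented as bearing out part of the hypothesis, and nothing in the text marks it as weaker evidence than the cough result.

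**Working it through.** **Step 1. Which endpoints belong to the hypothesis.** Combining the abstract's Discussion paragraph with the Introduction gives these items besides coughing and adverse events:

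1. remifentanil dose
2. failure rate (listed as success rate under Secondary endpoints; its complement, so one test)
3. haemodynamics
4. bronchoscopist satisfaction
5. anaesthesiologist satisfaction
6. patient satisfaction, reported by parents

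That is k = 6, or k = 8 if heart rate, systolic and diastolic pressure are tested separately. Procedure time and cough scores in the recovery unit appear in none of the hypothesis statements. Discharge time appears only in the Discussion, as an expected absence of effect. Adding these three gives k = 9, or k = 11 with the haemodynamic split.

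**Step 2. Inputs.** Alpha is 0.05 two-sided (Statistical analysis), so c = 1.96. The correlation ρ between test statistics is not given; I assume a common value and show 0, 0.5 and 0.8. All null hypotheses are taken as true. The plan states no family-wise figure of its own, so there is none to reproduce.

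**Step 3. Independent tests.**

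- Either direction: 1 − 0.95^6 = 1 − 0.735 = 0.265.
- Favouring rocuronium only: 1 − 0.975^6 = 1 − 0.859 = 0.141.

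**Step 4. Correlated tests.** Orient each statistic so that positive values favour rocuronium, and write Z_i = √ρ·U + √(1 − ρ)·E_i with U and E_i independent standard normal. Then

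- either direction: 1 − ∫ φ(u) [Φ((c − √ρ·u)/√(1 − ρ)) − Φ((−c − √ρ·u)/√(1 − ρ))]^k du
- favourable only: 1 − ∫ φ(u) [Φ((c − √ρ·u)/√(1 − ρ))]^k du

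Probability of at least one false positive, either direction, by numerical integration:

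| Tests | ρ = 0 | ρ = 0.5 | ρ = 0.8 |
|---|---|---|---|
| 6 (hypothesis items) | 0.265 | 0.21 | 0.14 |
| 8 (haemodynamics split) | 0.337 | 0.25 | 0.16 |
| 9 (all except adverse events) | 0.370 | 0.27 | 0.17 |
| 11 (all, haemodynamics split) | 0.431 | 0.30 | 0.18 |

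Favouring rocuronium only, k = 6: 0.14, 0.10 and 0.07.

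**Step 5. Effect of a correction.** Bonferroni over six tests uses 0.05/6 = 0.0083 per test. Under independence the chance of any false positive is then 1 − (1 − 0.0083)^6 = 0.049. Holm gives the same family-wise protection with no less power.

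**The case against.** The other side has four fair arguments.

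- **The primary inference is untouched.** There is one primary endpoint, the sample size is built on it, and the only stated rule for calling a conclusion robust concerns it. The Discussion introduces the remaining outcomes as additional comparisons, and the abstract says only that rocuronium may have these effects. This stands, and it limits the weight of the point.
- **A reader might infer that any secondary endpoint with p < 0.05 counts as confirmation even if cough frequency shows no difference.** No section says so. The text is silent on what follows from a null primary result; it does not grant that permission.
- **A reader might put the error rate at 27% to 30%.** That follows from 9 to 11 tests at correlation 0.5, a family that includes two outcomes not hypothesised and one expected to show no impact. It is not the figure for the hypothesis items at that correlation. About half of any such figure is also error against rocuronium, which nobody would report as benefit. Independence is close to a ceiling: under the procedure section, remifentanil is adjusted to coughing, and failure is defined by a supplementary rocuronium dose given when persistent coughing cannot be met with enough remifentanil.
- **Labels and test order are often left to the analysis plan, and 95% confidence intervals are already promised for the endpoints.** The second part is true and covers part of the remedy. The first does not answer the point, because the article itself fixes both the alpha and the scope of the adjustment.

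**Conclusion.** The point holds as a modest, inexpensive correction. The plan gives each of six hypothesised secondary endpoints its own two-sided 5% test and protects only adverse events. If all six nulls are true, the chance of at least one false positive is about 21% at correlation 0.5, with a range of 14% to 26.5% over correlations from 0.8 to 0. For results favouring rocuronium it is about 10% (7% to 14%), against 2.5% for a single test. Over all secondary endpoints other than adverse events, 9 to 11 tests, the two-sided range is 17% to 43%. These figures rest on an assumed common correlation, approximate normality of the test statistics and the absence of any true effect. The text itself, and not any one of these values, establishes the defect. The type I error for cough frequency is unaffected, so the documents do not support reading this as a flaw in the trial's main conclusion.

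**What to change.** In Statistical analysis, replace the blanket 5% statement with one of two rules.

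**(a) Exploratory secondaries.** The confirmatory two-sided 5% test applies to cough frequency only. All secondary endpoints are exploratory and reported as estimates with 95% confidence intervals. The abstract's Discussion paragraph, the Introduction and the Discussion are reworded so that the confirmatory claim concerns coughing alone.

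**(b) A few confirmatory secondaries.** Before unblinding, the sponsor names a short list of its own choosing. The list is tested in a fixed order, each test at two-sided 5% and stopping at the first non-significant result, or by Holm. Either is used only if cough frequency is significant. The remaining secondary endpoints are exploratory.

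The Benjamini-Hochberg step for adverse events can stay as it is.

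The cost is wording: no extra patients and no extra data. The downside is that some nominally significant secondary results could not be claimed as confirmed. The change should be made before unblinding, because afterwards it would look driven by the results.

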## Discussion

This randomized controlled trial will recruit a total of 140 children to evaluate the effects of low-dose rocuronium compared with normal saline placebo on the incidence of coughing during the FFB procedure. In addition, we will compare the cumulative remifentanil dose, the success rate of the FFB operation, hemodynamic variables, cough scores in the recovery room, procedure time, adverse events during the procedure and in the PACU (including desaturation, laryngospasm, sore throat, bradycardia or tachycardia, hypertension or hypotension), discharge time and satisfaction scores of the anesthesiologist, bronchoscopists and patients. We also monitor the neuromuscular function using TOF ratio after administration of 0.3 mg⋅kg^–1^ rocuronium, as well as at the end of the procedure.

Stimulation of the larynx and trachea, particularly in patients under light anesthesia, may elicit intense coughing and potentially lead to laryngospasm (7). Remifentanil, a short-acting opioid, represents an especially promising choice for managing coughing during flexible bronchoscopy procedures. Li et al. reported that remifentanil can be safely and effectively administered to children undergoing flexible bronchoscopy (9). Compared with traditional sedation using only propofol, the combination of remifentanil and propofol for FFB results in a significant reduction in coughing episodes, thereby improving procedural tolerance and patient comfort. Despite these benefits, the use of remifentanil may lead to cardiorespiratory complications (14). Studies have demonstrated that the incidence of such complications varies between 20% and 60%, depending on the type of procedure and the chosen medication regimen (6, 28).

The utilization of LMA for airway management during FFB was first introduced in 1989. Since then, it has been widely recognized as a safe and effective device for airway control in both adult and pediatric patients (16). Alon et al.’s study in adults demonstrated that the use of the LMA provides superior airway support, maintains stable oxygen saturation, and offers a more convenient access point during FFB (16). Suzen et al. demonstrated that performing flexible bronchoscopy via an LMA is a safe, straightforward and efficient technique for the management of tracheobronchial foreign bodies in pediatric patients (22). Eliezer and colleagues also reported the safety of using the LMA during FFB. None of their patients experienced any complications or disturbances in gas exchange, and oxygen saturation levels were consistently maintained within the range of 95%–100% (20).

Neuromuscular blocking agents are widely used as an anesthesia adjunct to facilitate tracheal intubation and mechanical ventilation, relax abdominal muscles, and ensure immobility during surgery (29, 30). Tips and tricks for anesthesia during pediatric rigid bronchoscopy indicate that neuromuscular blocking agents can be administered when blood pressure or other hemodynamic parameters preclude the administration of sufficient doses of anesthetic agents (31). In Dich et al.’s study, which involved 20 adult participants, total intravenous anesthesia with suxamethonium was demonstrated to be a safe technique for LMA-assisted FFB (19). A retrospective observational study conducted by Li et al. demonstrated that muscle relaxants and low-frequency conventional ventilation can be safely utilized in both flexible and rigid bronchoscopy procedures for patients with chronic airway obstruction. They found that no patients experienced ventilation failure, bronchospasm, or intraoperative coughing (23). The role of neuromuscular blocking agents in FFB remains incompletely understood. To our knowledge, this will be the first randomized controlled trial to evaluate whether the adjunctive use of low-dose rocuronium in combination with remifentanil during LMA-assisted FFB in children leads to reduced coughing, a lower remifentanil dosage, more stable hemodynamics, no impact on discharge time, and increased satisfaction among anesthesiologists, bronchoscopists and parents. The selection of rocuronium over cisatracurium represents a deliberate choice based on the specific requirements of this trial. Rocuronium at 0.3 mg⋅kg^–1^ provides a rapid-onset, moderate-depth neuromuscular blockade whose duration approximates the typical procedure time. Given the availability of sugammadex, the duration of action becomes both flexible and controllable. Any residual blockade at the end of the procedure can be fully reversed within 2–3 min. However, we acknowledge that cisatracurium offers theoretical advantages, including organ-independent metabolism and a recovery profile less influenced by temperature or hepatic and renal function. In the context of this study conducted in healthy children undergoing brief procedures with active temperature management, these advantages are considered less critical than the practical benefits of rocuronium. In addition to reducing coughing and providing improved operating conditions, the use of low-dose rocuronium may allow for a reduction in the doses of remifentanil required to achieve adequate procedural conditions. Such a reduction could translate into faster emergence from anesthesia, fewer respiratory complications in the PACU, and an overall enhanced recovery profile. For our pediatric patients, intravenous propofol at a dose of 3 mg⋅kg^–1^ in combination with remifentanil at 3 μg⋅kg^–1^ will be utilized for induction. This will be followed by the administration of either 0.3 mg⋅kg^–1^ of rocuronium or an equivalent volume of normal saline. Sevoflurane will be titrated to achieve the appropriate depth of anesthesia, while remifentanil will be continuously infused. A LMA with an interface is inserted to guide the fiberscope passage while allowing uninterrupted ventilation and maintaining oxygenation.

This study has several limitations. First, despite variations in operation times, with some even exceeding the metabolic time of rocuronium, a uniform dose of 0.3 mg⋅kg^–1^ will be administered to all children. This decision was made to minimize the risk of delayed spontaneous breathing recovery due to incomplete metabolism of muscle relaxants. Second, children younger than 1 year will be excluded, as the cross-sectional area of the airflow channel in the LMA designed for this age group may be insufficient to accommodate the flexible bronchoscope. Third, the initial real-time assessment on coughing episode brings about the possibility of observer bias. We alleviated this issue by using predefined, measurable criteria and having the assessment conducted by a single-blinded observer. Nevertheless, the potential for variability in clinical judgment still remains a limitation of the assessment method. The operational definition of the cough-free interval, while clear in principle, presents a practical measurement challenge. To mitigate the impact of potential misclassification, we employed pre-planned sensitivity analyses using extreme re-definitions of an episode. The consistency of our primary finding across these alternative analyses supports the conclusion that any measurement noise introduced by the real-time application of the 3-s rule is unlikely to account for the observed treatment effect. Fourth, our protocol utilized BIS monitoring as an adjunct to clinical assessment. While this provides an additional objective parameter, the interpretation of BIS values in children requires caution. The algorithm’s validation is less established in children than in adults, and values can be influenced by physiological and pharmacological factors not necessarily indicative of cortical suppression of airway reflexes. Our hierarchical management protocol, which prioritized clinical signs over BIS values, is designed to mitigate this limitation. However, the inherent variability and potential inaccuracy of BIS in this pediatric population mean it could not serve as a perfect surrogate for reflex suppression, and this constitutes a limitation of the monitoring methodology. Fifth, patient satisfaction is reported by parents or guardians rather than by the children themselves, it represents a proxy assessment of the caregiver’s perception of the child’s experience and their own experience of the process. While this is a common and practical approach in pediatric research involving young children, it may not directly correlate with the child’s self-assessed experience, especially for non-verbal or pre-verbal children. Therefore, while this measure provides valuable insight into a key stakeholder’s perspective, it should not be equated with patient-reported outcomes in older, cognitively capable populations. This study enrolls children with active pneumonia or airway foreign body, nearly all of whom may present with a cough. To isolate the effect of the intervention on procedure-induced coughing, we exclude children who have an acute, subjective exacerbation of cough (a ≥2-fold increase) prior to the procedure. This operational definition, although relying on parental report, offers a practical threshold for identifying children with unstable airway symptoms. Nevertheless, the baseline level of airway inflammation and irritability caused by pneumonia or foreign body itself remains a potential confounding variable. We record the baseline cough frequency to ensure balance between groups through randomization and set it as a covariate. We also acknowledge that the background “cough propensity” stemming from the underlying disease is an inherent limitation when studying this clinically relevant endpoint. Even with its predefined constraints, this study will provide the first randomized evidence on the efficacy and safety of this specific adjuvant technique. The findings from this trial should pave the way for more nuanced investigations. Future studies could explore weight- or time-adjusted dosing regimens of rocuronium to optimize the balance between efficacy and recovery. Furthermore, our work highlights the need for the development of specialized LMAs with larger airway channels suitable for infants, which would allow subsequent research to include this vulnerable age group and create a comprehensive clinical guideline across all pediatric ages.
